### *Secondary Outcome Measures*

The secondary outcome measures will be the time to complete a standard tn-ECHO assessment, which will be defined when ultrasound images have been acquired for all four cardiac views (see appendix), the total number of times solutions are given to the infants, and the quality of images.

Quality of tn-ECHO images: The quality of tn-ECHO images will be rated by 2 neonatologists/cardiologists blind to the treatment groups and to any clinical information about each patient. A scale for rating the overall quality was designed (attached) in consultation with the Cardiology Department. Before the start of the study, a pilot of 10 tn-ECHOs will be rated to ensure starting inter-rater reliability is achieved (agreement > 85%). Then, inter-rater reliability will be checked between raters after ½ the study patients are enrolled. Inter-rater reliability will be assessed using the Bland and Altman approach which analyzes the differences in scores between two coders over the pair-wise mean of the two coders.

### **Other Data Collected**

We will collect clinical information regarding the infant from birth to day of testing including but not limited to the following: birth weight, GA at birth, Apgar score at one minute, illness severity, head scans/MRI results, respiratory support, medications, type and time of last handling just before tn-ECHO. Much of this data will be used for descriptive purposes.

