## **Inclusion Criteria**

Infants born between 26-42 weeks of gestational age admitted to the Neonatal Intensive Care Unit and Intermediate Nursery at Children's and Women's Health Centre of British Columbia (C&W) who are stable enough to have a tn-ECHO. To avoid bias in completing time of the tn-ECHO we have excluded purely educational studies.

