## **Exclusion Criteria**

Infants who have congenital anomalies, or a lethal condition in whom intensive care is not indicated; infants who have received analgesics or sedatives within 72 hours of the assessment; history of maternal abuse of controlled drugs and substances. Infants who are too unstable to be exposed to a tn-ECHO or who already have an ECHO performed by a Pediatric Cardiologist within 4 hours. Inability to obtain parental consent (due to language barrier, etc.).

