## **Procedures**

All testing will take place in the NICU and Intermediate Nursery at C&W. As in our previous studies, five minutes before, during and five minutes after the tn-ECHO procedure, a close up image of each infant's face and upper extremities are videotaped. The digital, color camera is set up using a tripod. Using a foot pedal attached to the camera, recordings are synchronized to mark events. These tapes will be used to provide blinded behavioral coding of our primary outcome measure in conjunction with our bedside scoring described below.

For all groups, each infant will remain in his/her incubator/cot, positioned with rolls around the body to promote a flexed position. Every attempt will be made to have the procedure scheduled one hour post feed, if the infant is feeding. After a 20 minute rest period, five minutes before the contact of the physician to conduct the examination, an attending physician who is not conducting the tn-ECHO will assess the infant's baseline stress levels over a 30 second period using the Behavioral Indicators of Infant Pain (BIIP). BIIP score will then be measured 2 min after first administration of the solution (at time of starting of the tn-ECHO), then halfway through the assessment (as defined per echocardiographical images obtained, after completion of the right ventricular long axis view with RVO), and finally immediately after the last contact of the physician.

With respect to the glucose/water administration, two minutes before the first contact by the physician performing the tn-ECHO, each infant will be given either 0.5ml of 25% glucose (26-31 weeks gestational age group) or 1.0 ml of 25% glucose (32-42 weeks gestational age group). The solution will be applied to the anterior portion of the tongue followed by insertion of a soother. The soother will be held in the infant's mouth to ensure that continuous contact is maintained throughout the testing period. During the course of the assessment (estimated about 20 min), this application can be repeated if necessary (if the infant's movements interfere with the quality of picture obtained) to a maximum of four times, adding up to max 2ml of 25% glucose in the 27-31 weeks gestational age group or 4ml of 25% glucose in the 32-40 weeks gestational age group. During each tn-ECHO, infants have additional handling only if it is required to maintain physiological stability. Pharmaceutical interventions are an exclusion criterion for the study.

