## **Statistical Analyses**

Demographic and medical information about the infants will be compared between groups to ensure balance. Then, the primary outcome for analysis will be defined as the between group difference between average BIIP scores in the pre and during echocardiography observations. Mean change scores will be calculated and a 2 Group (Intervention) by Phase (Baseline, Echo) analysis of variance will be used to determine main effects. The confidence interval for the difference in treatment effects will be of primary interest. Any differences in baseline BIIP scores or medical/demographic variables found would be included as co-variables in the analysis. Differences between tn-ECHO times between groups, in the total number of times solutions are administered for each group, and in the overall quality ratings of the tn-ECHOs will be compared using paired t tests.

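### Age enters the model only if the groups happen to differ on it, and the only age named is gestational age at birth; prespecifying postmenstrual age at the scan would be the stronger choice

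*Protocol*

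**What the plan says.** - **Inclusion Criteria (Protocol).** Eligibility is by age at birth: "Infants born between 26-42 weeks of gestational age". The only condition bearing on when the scan happens is clinical: infants "who are stable enough to have a tn-ECHO". Neither this section nor Exclusion Criteria limits postnatal or postmenstrual age at the scan.
- **Other Data Collected.** The age named is gestational age at birth ("birth weight, GA at birth, Apgar score at one minute"). The list is open and extends to the test day: "from birth to day of testing including but not limited to the following".
- **Statistical Analyses.** No age covariate is named. The rule is: "Any differences in baseline BIIP scores or medical/demographic variables found would be included as co-variables in the analysis".
- **Methods.** Randomisation uses permuted blocks of four and six. No stratification by age is stated.
- **Sample Size Estimate.** The recruitment target already allows for one or two covariates, with baseline behavioural state as the example.
- **Procedures.** The first-dose volume depends on age band, for example "0.5ml of 25% glucose (26-31 weeks gestational age group", without saying whether that is age at birth or at the scan. The bands are labelled 26-31 and 32-42 weeks for the first dose, but 27-31 and 32-40 weeks for the maximum total.

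**The concern.** The BIIP is scored from facial actions, hand actions and sleep/wake state. Such behaviour plausibly depends on how mature the infant is when tested. Maturity at testing is postmenstrual age: gestational age at birth plus postnatal age. With no limit on postnatal age, two infants of equal maturity at the scan can differ by many weeks in gestational age at birth.

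The Statistical Analyses section does not settle the matter in advance. A variable is adjusted for when the groups are seen to differ on it, and otherwise left out. Two weaknesses follow. A prognostic variable that happens to be balanced is omitted, so its variance stays in the error term. And the model is fixed only after the data have been inspected, with no definition of what counts as a difference. At stake are the width of the confidence interval, which the protocol calls its primary interest, and protection against chance imbalance in groups of about 26 (104/4).

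**Working it through.** The protocol gives no figure to reproduce here, so the check is a reading of the text plus a sensitivity calculation.

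**Inputs**
- Gestational age at birth: 26-42 weeks (Inclusion Criteria), taken as uniform. *Assumption.* Variance = 16²/12 = 21.33.
- Postnatal age at the scan: not in the protocol. Taken as exponential with mean m weeks and independent of gestational age at birth. *Assumption.* Variance = m².
- R², the share of variance in BIIP change explained by postmenstrual age at the scan: not in the protocol. Range 10-20%. *Assumption.*
- Gestational age at birth is taken to predict BIIP change only through its correlation r with postmenstrual age. *Assumption.*

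**Step 1. Gain against no age term** (the default unless a difference is found). Residual variance falls by the factor 1 − R², so

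gain in effective sample size = 1/(1 − R²) − 1

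- R² = 0.10: 1/0.90 − 1 = 11%
- R² = 0.20: 1/0.80 − 1 = 25%

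This does not depend on when scans are done.

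**Step 2. How well gestational age at birth stands in for age at the scan.**

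r² = 21.33/(21.33 + m²)

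- m = 1: 21.33/22.33 = 0.955, r = 0.98
- m = 2: 21.33/25.33 = 0.842, r = 0.92
- m = 4: 21.33/37.33 = 0.571, r = 0.76

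**Step 3. Gain against adjusting for gestational age at birth.**

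gain = (1 − R²r²)/(1 − R²) − 1 = R²(1 − r²)/(1 − R²)

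| Mean postnatal age | 1 − r² | R² = 0.10 | R² = 0.20 |
|---|---|---|---|
| 1 week | 0.045 | 0.5% | 1.1% |
| 2 weeks | 0.158 | 1.8% | 3.9% |
| 4 weeks | 0.429 | 4.8% | 10.7% |

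**Step 4. If earlier-born infants are scanned later.** Take mean postnatal age as half the weeks remaining to 40 (zero after 40), still exponential. The overall mean is (14/16) × 3.5 = 3.06 weeks, the variance of postnatal age is 19.20 and its covariance with gestational age at birth is −10.21. Then

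r = (21.33 − 10.21)/√[21.33 × (21.33 + 19.20 − 2 × 10.21)] = 11.12/20.7 = 0.54

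and the gain is about 8% (R² = 0.10) to 18% (R² = 0.20). So the independence assumption in Steps 2-3 is favourable to gestational age at birth.

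**Step 5. Cost.** With 104 infants in four groups, one more term takes one of about 104 − 4 = 100 residual degrees of freedom.

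**Step 6. Volume bands, by reading.** An infant born at 31 weeks and scanned at 3 weeks of age, and one born at 32 weeks and scanned at 2 weeks, are both at 34 weeks. If the bands mean age at birth, they fall in different bands; if they mean age at the scan, they do not. The text does not say which.

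**The case against.** **The variable is available and no wrong adjustment is specified.** A reader might infer that any age adjustment would be forced onto gestational age at birth. The text does not support that: the data list is open and runs to the day of testing, age at the scan can be derived, and the protocol commits to no age adjustment. This objection stands in full.

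**Covariate detail belongs in the SAP.** In part. The exact form of a term can be left there, and not naming age at the scan in the data list is only missing detail. But the protocol states a rule for choosing covariates, and a stated rule can be judged.

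**Randomisation balances maturity.** It does, in expectation. A reader might infer that the treatment comparison is biased; it is not. Only precision, chance imbalance and interpretation are affected.

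**The gain may be small.** This stands. No passage gives R². The outcome is a within-infant change, which already removes stable differences in BIIP level, so R² could be below 10%. Large gains over gestational age at birth require late scans, or earlier-born infants being scanned later, and the protocol documents neither.

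**The bands may be harmless.** A reader might infer that equally mature infants will receive different volumes. That holds only on a birth-age reading, and whether it would matter is a clinical judgement outside this review. What stands is the undefined age basis and the two sets of labels.

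**Conclusion.** The point holds as a modest improvement to the analysis. Eligibility is by age at birth, age at the scan is unlimited, and an age term enters the model only through an observed group difference. A prespecified term for postmenstrual age at the scan is better than that rule.

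If age at the scan explains 10-20% of the variance in BIIP change, the gain is about 11-25% in effective sample size over no age term. Over gestational age at birth it is about 2-4% (mean postnatal age 2 weeks) or 5-11% (4 weeks), somewhat more if earlier-born infants are scanned later, and near zero if scans come in the first days of life. All of these rest on assumed values of R² and postnatal age. The direction is secure; the size is not. No bias between arms is shown and no data are lost.

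The inconsistent band labels and undefined age basis in Procedures are a separate matter of clarity.

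**What to change.** 1. **Statistical Analyses:** name postmenstrual age at the scan as a continuous covariate in the primary model, whatever the observed balance, instead of choosing an age variable after seeing the groups.
2. **Other Data Collected:** add postmenstrual age at the scan to the list.
3. **Procedures:** state which age the volume bands refer to, and reconcile the 26-31/32-42 and 27-31/32-40 week labels. The sponsor must decide this; no basis or volume is proposed here.

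Cost: one line in the data list, no new measurement, and one model degree of freedom, which fits within the one or two covariates that the Sample Size Estimate already allows for.

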### **Sample Size Estimate**

In infant studies where self-report is not possible, a 2 point difference in pain scores has been considered clinically significant (10% reduction). Twenty five infants per group (100 total) will yield 80% power for a difference corresponding to the anticipated difference of 2 points on the

BIIP scale between treatment groups. Allowing for potential attrition of 10% and the need for including one or two co-variables in the analysis (e.g. differences in behavioral state at baseline), we may need to recruit up to 115 infants.

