## **Methods**

Parents will be asked for written informed consent prior to randomization. It is not standard of practice to obtain parental consent for procedures like echocardiography that are clinically indicated; therefore, the consent will be purely for research purposes.

One hundred and four infants will be randomized to one of four intervention groups (Grp 1: glucose + soother; Grp 2 glucose + soother + facilitated tucking; Grp 3: water + soother; Grp 4: water + soother+facilitated tucking) which will take place during a single tn-ECHO examination, at the discession and after consultation with the medical team.

Randomization to each group will be determined by generating randomly permuted sequential blocks of four and six allocation numbers. The Clinical Services Research Unit will initiate the randomization process and provide the information regarding group allocation that will guide the intervention. Access to the randomization list will be through a web-based system that will enable online interactive checking of the inclusion/exclusion criteria before authorizing random allocation. This system is very reliable with 24-hour on-line support; as part of the data management services, a person will be available by phone during working hours at C&W to provide back-up for the system for unanticipated events. Randomization and preparation of the solutions will then be done by the pharmacist on site who will provide the solutions in unmarked syringes containing 5ml of either water or 25% glucose.

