## **Outcome Measures**

### *Primary Outcome Measure*

The primary outcome measure will include changes in BIIP scores across phases (Baseline, maximal score at first contact by physician, ½ through the tn-ECHO, Recovery) of the study. The Behavioral Indicators of Infant Pain (BIIP) is a reliable and valid scale we developed for assessing acute procedural pain in preterm infants, although it can also be used for measuring stress.

The BIIP combines into a single scale changes in sleep/wake states, five facial actions and two hand actions. The scoring sheet is appended. Scores range between 0-9, with scores 0-2 indicating mild or no pain/stress, 3-6 indicating moderate pain/stress and scores 7-9 indicating more severe pain/stress. In response to heel lance, under conditions where no intervention is provided, mean scores on the BIIP were  $5.3 \pm 2.6$  points. For less intrusive, but stressful procedures, such as diaper change, mean BIIP scores were  $3.1 \pm 0.5$ . To ensure reliability for

BIIP coding, physicians will be trained by [name] to achieve inter-rater reliability on the scale to above 0.85 (kappa). After the first 20 sessions, inter-rater reliability will be checked using the Bland and Altman approach which analyzes the differences in scores between two coders over the pair-wise mean of the two coders.

From the bedside videotapes, using the Noldus Observer system^16, one, 30-second block will be coded in real-time across four procedure phases:

|            |                                                                     |
|------------|---------------------------------------------------------------------|
| Baseline   | [T0] = 30 seconds, 5 minutes before first contact by the physician, |
| Time 1     | [T1] = 30 seconds beginning 2 minutes after first solution given,   |
| Time 2     | [T2] = 30 seconds after 4 and 5 chamber views finished              |
| Recovery 2 | [T3] = 30 seconds after the last contact by the physician           |

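### The 2-point target is labelled 10% but is 22% of the BIIP range, and 104 randomised less the planned 10% attrition leaves about 94, short of the 100 behind the stated 80% power

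*Protocol*

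**What the plan says.** **Target difference.** The Protocol, Sample Size Estimate, states that "a 2 point difference in pain scores has been considered clinically significant (10% reduction", citing a source on pain assessment in infants. It then takes 2 points on the BIIP as the anticipated difference between treatment groups.

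**Scale.** Under Primary Outcome Measure, the BIIP is described with "Scores range between 0-9". Two reference values follow: 5.3 ± 2.6 for heel lance without intervention, and 3.1 ± 0.5 for diaper change. The protocol does not say whether the ± values are SDs, and it ties neither to the sample size.

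**Numbers.** Sample Size Estimate: "Twenty five infants per group (100 total) will yield 80% power". The same section continues "Allowing for potential attrition of 10% and the need for including one or two co-variables in the analysis", and concludes that "we may need to recruit up to 115 infants". Methods says: "One hundred and four infants will be randomized", in four groups.

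**Analysis.** Study Design calls the trial factorial with four arms. Statistical Analyses plans an analysis of variance on mean change scores, intervention by phase, to determine main effects. The power statement names no SD, significance level, sidedness or contrast.

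**The concern.** The percentage is part of the argument that 2 points is the right difference to look for. If it is wrong for the BIIP, a reader takes the trial to be sized for an effect less than half as large, relative to the scale, as the one actually used.

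The randomised number matters because the power claim is tied to 25 infants per group. If Methods randomises too few to leave 25 per group after the protocol's own attrition, the trial as written does not deliver the claim. With SD and contrast unstated, neither the 80% nor the effect of a shortfall can be read from the protocol.

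**Working it through.** **1. The percentage**
- Share of the range: 2/9 = 22.2%.
- Share of the heel-lance mean: 2/5.3 = 37.7%.
- Share of the diaper-change mean: 2/3.1 = 64.5%.
- Ten per cent of the BIIP range would be 0.1 × 9 = 0.9 point. Two points is 10% only of something about 20 points wide (2/0.10 = 20).

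**2. The number randomised**
- Needed for analysis: 4 × 25 = 100.
- With 10% attrition: 100/(1 − 0.10) = 111.1, so 112. The further allowance for covariates takes this plausibly to the ceiling of 115.
- From Methods: 104 × 0.90 = 93.6, or 23.4 per arm.
- Loss that 104 can absorb before falling below 100: 4/104 = 3.8%.

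**3. The 80%**

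The plan's figure cannot be strictly reproduced because its inputs are not given. *Assumptions:* two-sided 5%, comparison of two arms, and the ± values read as SDs.

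Formula: noncentrality = 2 / (SD × √(2/n)), with n per group. Power comes from the normal approximation (z) or the noncentral t (t).

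- The SD that gives exactly 80% at 25 v 25 is 2.52 (z) or 2.47 (t).
- With SD 0.5, noncentrality at 25 v 25 is 2/(0.5 × √(2/25)) = 14.1 and power is essentially 100%, so this spread was not the input.
- With SD 2.6:

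| Comparison | SE = 2.6 × √(2/n) | Noncentrality | Power, z | Power, t |
|---|---|---|---|---|
| 25 v 25 (100 analysed) | 0.735 | 2.72 | 77.6% | 76.0% |
| 23.4 v 23.4 (104 less 10%) | 0.760 | 2.63 | 74.9% | 73.1% |
| 50 v 50 (main effect, 100 analysed) | 0.520 | 3.85 | 97.0% | 96.8% |
| 46.8 v 46.8 (main effect, 104 less 10%) | 0.537 | 3.72 | 96.1% | 95.7% |

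The main-effect rows assume that the 2-point difference holds on average over the levels of the other factor.

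**4. Change scores**

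Statistical Analyses uses change from baseline. If the SD is 2.6 in each phase and r is the correlation between baseline and echo scores, the SD of change is 2.6 × √(2(1 − r)). The protocol gives no r, so a range is shown (t):

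| r | SD of change | Power 25 v 25 | Power 50 v 50 |
|---|---|---|---|
| 0 | 3.68 | 47% | 77% |
| 0.3 | 3.08 | 62% | 90% |
| 0.5 | 2.60 | 76% | 97% |
| 0.7 | 2.01 | 93% | >99% |

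The unstated correlation moves pairwise power far more than the loss of six infants does.

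**The case against.** Several stronger readings are tempting, and the document does not support them.

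**Three conflicting totals.** A reader might infer that 100, 104 and 115 all contradict each other. They do not: 100 is the number needed for analysis, and 115 is a recruitment ceiling after attrition and covariates. Only 104 is out of line. It might be what remains of 115 after losses between consent and randomisation (115 × 0.9 = 103.5). In that case 26 per arm would be analysed and the shortfall would vanish. The protocol does not say so, and the point about 104 rests on attrition occurring after randomisation.

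**The 80% is wrong.** A reader might infer that it fits no spread in the protocol. A spread of 2.6 nearly reproduces it: 27 per group (z) or 28 (t) against 25 stated, with power 2 to 4 percentage points low. A four-group F test with one arm 2 points away gives 79.0%, and baseline adjustment at an assumed correlation of 0.3 gives 79.8%. What stands is that the claim cannot be verified.

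**The trial is underpowered.** On pooled main effects at SD 2.6, power is well above 80% even with about 94 infants, so the shortfall matters for pairwise comparisons only.

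**The 10% drives the sample size.** It does not, because 2 points is the input. The parenthesis is attached to pain scores in general and may be right for whatever scale the cited source used, which cannot be seen here. The fault is carrying it over to a 0-9 scale. Nor does the protocol set 0.9 point as a target, so low power for that difference is no failure of the plan.

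**Conclusion.** Two points hold on the protocol's own figures. Two BIIP points is 22% of the range and not 10%, so the stated justification of the target difference is wrong for this scale, while the sample size is unaffected. And 104 randomised with 10% attrition leaves about 94 infants, 6 short of the 100 behind the power statement and 8 fewer randomised than the 112 that it implies. The second point assumes that the attrition falls after randomisation.

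A third point is one of verification: the 80% has no named SD, alpha or contrast. Under the assumption of SD 2.6 and two-sided 5%, the shortfall costs about 3 percentage points of pairwise power (76-78% down to 73-75%) and about 1 point for main effects, which stay near 96%. These figures illustrate the size of the issue and are not estimates of the trial's true power, since they shift with the baseline correlation once change scores are analysed.

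**What to change.** 1. In Sample Size Estimate, delete the 10% parenthesis, or state that 2 points is 22% of the BIIP range.
2. Give one randomised number in Methods and Sample Size Estimate, and say whether the 10% attrition is counted before or after randomisation.
3. Restate power at the evaluable number that follows (about 94 if 104 stays and losses fall after randomisation), for the contrast in Statistical Analyses, with alpha and sidedness. State whether that contrast is a pooled main effect or a pair of arms.
4. Have the sponsor name and justify an SD for the analysed change score. The 2.6 should not simply be written in: it is an unlabelled spread from untreated heel lance, a skin-breaking procedure, and it is not the SD of a change score.

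**Cost:** protocol wording only. The stated pairwise power may become slightly less favourable. No extra infants are required. If the sponsor prefers to keep 100 evaluable, 112 randomised already lies within the ceiling of 115.
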